### Randomization

Participants will be randomly assigned (1:1 ratio) to the CFT or Therapeutic Exercises groups (Fig 1). An independent researcher will carry out the randomization using a computer-generated sequence from http://www.randomization.com, stratified by age (<or ≥ 50 years) and sex (female or male), with group assignments concealed in consecutively numbered, sealed, opaque envelopes. These envelopes will be securely stored and opened sequentially by an independent researcher before the first session, ensuring allocation concealment.

**Fig 1 pone.0320025.g001:**
[figure not shown]
Diagram of participant flow.

### Blinding

The assessor and statistician will be blinded to treatment group assignments. Participants will be treated individually and not be informed of the study hypothesis. No circumstances have been established that would allow unblinding.

### Procedures

Baseline assessments will include the characteristics of the participants, such as sociodemographic data (e.g., sex of birth, age, height, weight, body mass index, occupation, education level, upper limb dominance, physical activity characteristics) as well as information related to shoulder pain (e.g., painful side, duration of symptoms, pain intensity, use of medication, influence of pain on work, leisure activities, and sleep, and details of previous treatments). The self-reported most painful shoulder will be considered for all outcome measures for individuals with bilateral symptoms. Outcome measures will be assessed at baseline, 4-week, at the end of treatment (8-week), and 12-week follow-up, except patients’ expectations of treatment, which will be measured only at baseline, and perception of improvement/deterioration, which will be measured at 4-week, 8-week, and 12-week follow-ups (Fig 2). Patients’ treatment expectations will be assessed using the question “How much do you expect your shoulder to improve at the end of treatment?”. The score will be measured on a 7-point Likert scale, where 1 corresponds to “the worst possible” and 7 corresponds to “fully recovered”. This assessment will be conducted before the intervention begins. Patient expectations are a significant predictor of treatment outcomes, as demonstrated by a study evaluating individuals with shoulder pain [43].

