### Data analysis

Statistical analysis will be conducted using the Statistical Package for the Social Sciences (SPSS) version 24.0 or a more recent version (SPSS Inc., Chicago, IL). Continuous data will be summarized as means ± standard deviation (SD) and 95% confidence intervals (CIs). Data normality will be assessed through visual inspection of histograms and the Shapiro-Wilk test. The analysis will adhere to the intention-to-treat principle. Between-group differences (treatment effects) and their corresponding 95% CIs will be computed using linear mixed models with Bonferroni adjustments. If non-normality of the data is identified, transformations will be performed as needed or generalized linear mixed models will be considered. Fixed effects will include group, time, and the group-by-time interaction. Random effects will account for individual variability. A significance level of 0.05 will be applied for all statistical tests.

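### Baseline treatment expectation, which the protocol calls predictive of outcome, is not named in the mixed model; pre-specifying it with a time interaction is a cheap, modest gain (minor)

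*Protocol article*

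**What the plan says.** Under Procedures, the protocol article describes a single expectation question answered before treatment. On the scale: "The score will be measured on a 7-point Likert scale". On the schedule, it stands apart from the other measures: "except patients’ expectations of treatment, which will be measured only at baseline". The reason given for collecting it is that "Patient expectations are a significant predictor of treatment outcomes", with one cited shoulder-pain study in support and no correlation or other measure of strength.

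Under Data analysis, treatment effects are between-group differences with 95% confidence intervals from linear mixed models. The model terms are described in two sentences: "Fixed effects will include group, time, and the group-by-time interaction" and "Random effects will account for individual variability". No baseline covariate is named. Expectation is also absent from the outcome table (Table 2) and is not a stratification factor; randomisation is stratified by age and sex only.

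On timing, Procedures says of the expectation item: "This assessment will be conducted before the intervention begins". Under Randomization, the envelopes are "opened sequentially by an independent researcher before the first session". The text does not say in words which of the two comes first.

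**The concern.** A variable that the protocol itself describes as prognostic will be in hand for every participant, yet the stated model does not use it. Adjusting for a truly prognostic baseline variable usually narrows the confidence interval. It also removes the part of the observed difference that comes from one arm happening to start with higher expectation. Both considerations apply here: the trial is small (36 per arm), expectation is not balanced by design, both primary outcomes are self-reported, and the Strengths and limitations section says participants cannot be blinded.

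What is at stake is precision, and how close the estimate lies to the truth in the one sample drawn. Validity is not at stake. A second, conditional matter is that the score is a sound covariate only if it is taken before the participant can know the arm. An answer given after disclosure could depend on the allocation.

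**Working it through.** **Inputs.** SPADI difference 18, SD 24.6, two-sided alpha 0.05, power 80%, dropout 15% (Sample section). Correlation *r* between expectation and the analysed outcome, given the other model terms: not in the documents, so assumed at 0.1 to 0.4.

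**1. The plan's own figure.** n per arm = 2 × (1.960 + 0.842)² × 24.6² / 18² = 29.3, rounded up to 30. With dropout, 30 / 0.85 = 35.3, rounded up to 36 per arm, 72 in total. This matches the protocol and uses no covariate gain.

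**2. Precision at a single visit.** With 30 completers per arm the unadjusted SE is 24.6 × √(2/30) = 6.35. Adjustment multiplies it by √(1 − r²):

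| Assumed r | SE (SPADI points) | 95% CI half-width | Fall in SE |
|---|---|---|---|
| 0 (unadjusted) | 6.35 | 12.45 | – |
| 0.1 | 6.32 | 12.39 | 0.5% |
| 0.2 | 6.22 | 12.20 | 2.0% |
| 0.3 | 6.06 | 11.88 | 4.6% |
| 0.4 | 5.82 | 11.41 | 8.3% |

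The percentages do not depend on the SD, so they apply equally to NPRS at the same r.

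**3. Chance imbalance.** With 36 per arm, the between-arm difference in standardised expectation has SD √(2/36) = 0.236. The probability that it exceeds 0.3 SD in either direction is about 20%. An imbalance of that size moves the SPADI difference by 0.3 × r × 24.6 points: 0.7 at r = 0.1, 2.2 at r = 0.3 and 3.0 at r = 0.4, against a planned 18.

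**4. Which contrast gains.** Baseline is one of the four visits, so the effect may be read as a difference at a visit or as a group-by-time contrast from baseline. Write a main effect of expectation as βx. In outcome(t) − outcome(0) the term βx − βx vanishes, so with balanced data a main effect alone cannot alter the second contrast. With an interaction the term is (β_t − β_0)x, which matters only if expectation predicts change.

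A small simulation agrees (60 participants, four complete visits, random intercept, standardised outcome, slope 0.3 on expectation after baseline, 40 data sets). Mean SEs for week 8:

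| Scenario and contrast | No expectation | Main effect only | With time interaction |
|---|---|---|---|
| Slope 0.3 at all visits: group difference | 0.2516 | 0.2375 | 0.2383 |
| Slope 0.3 at all visits: change from baseline | 0.2524 | 0.2524 | 0.2545 |
| Slope 0 at baseline, 0.3 after: group difference | 0.2421 | 0.2352 | 0.2337 |
| Slope 0 at baseline, 0.3 after: change from baseline | 0.2584 | 0.2584 | 0.2549 |

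The main effect alone left the change contrast identical to rounding error (differences of order 10⁻¹⁵). With the interaction, the SE of the group difference fell by about 5% (0.2516 to 0.2383) in the first scenario and 3.5% (0.2421 to 0.2337) in the second. The SE of the change contrast fell by about 1.4% where expectation predicted change, and rose by about 0.8% where it did not.

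**The case against.** The strongest reply is that nothing here is wrong. Recording a prognostic characteristic does not commit a trial to model it, and the two sections are compatible. Randomisation keeps the unadjusted estimate unbiased, and its confidence interval already allows for chance imbalance. The list of fixed effects says what the model will include, which need not exclude further terms, and an analysis plan that is not shown may add them. The strength of the association rests on a cited study that the documents do not quantify. All of this stands, and it is why the point is minor.

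Three stronger readings are tempting and are not supported:

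- **That the primary analysis is biased or underpowered.** It is neither: the 72 reproduces without adjustment.
- **That adjustment would buy a definite amount of power.** For one visit with 30 completers per arm, a normal approximation gives 80.9% unadjusted and 87.1% at r = 0.4. That is a single-timepoint comparison under an assumed correlation. It is not the planned mixed model, and it does not carry over to change from baseline.
- **That the score is taken after allocation is known.** The protocol places it at baseline only, which suggests the right order. The participant-flow and schedule figures, which may settle it, are not available here.

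What remains is that the article does state its model, gives the score no analytic use, and could name it at almost no cost.

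**Conclusion.** The point holds as a missed improvement of minor priority. The model as stated forgoes a reduction in SE of about 0.5% to 8% for between-group differences at a visit, if the residual correlation lies between 0.1 and 0.4; at 0.2 or below the gain is negligible. It also forgoes protection against a chance imbalance that, at 0.3 SD and r = 0.3, would move the SPADI difference by about 2.2 points. For contrasts of change from baseline, any gain depends on expectation predicting change. The correlation is an assumption throughout, and the simulation is illustrative, with complete data and a random intercept only. The timing question is a condition on the fix, since the analysis as stated does not depend on it.

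**What to change.** - **Data analysis:** pre-specify baseline expectation (1 to 7, linear) and its interaction with time as fixed effects in the mixed models for SPADI and NPRS. The interaction lets both visit-specific differences and change-from-baseline contrasts benefit.
- **Procedures:** confirm that the expectation score is recorded before the allocation envelope is opened.

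With four visits the two terms use 1 + 3 = 4 fixed-effect parameters per outcome. The change needs two sentences and no new data. Fixing it now also avoids choosing between adjusted and unadjusted models once results are known.

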**Fig 2 pone.0320025.g002:**
[figure not shown]
Schedule of enrolment, interventions, and assessments.

### Outcomes measures

The outcomes and outcome measures are presented in Table 2.

**Table 2 pone.0320025.t002:** Summary of outcome measures.

Outcome Measure	Type of Data	Scale	Unit of Measurement
**Primary Outcomes**			
Numerical Pain Rating Scale (NPRS)	Continuous	Ordinal (0–10)	Points
Shoulder Pain and Disability Index (SPADI)	Continuous	Interval (0–100)	Percentage (%)
**Secondary Outcomes**			
Patient-Specific Functional Scale (PSFS)	Continuous	Interval (0–10)	Points
Pain Self-Efficacy Questionnaire (PSEQ)	Continuous	Interval (0–60)	Points
Pittsburgh Sleep Quality Index (PSQI)	Continuous	Interval (0–21)	Points
Brief Screening Questions for Biopsychosocial Aspects	Continuous	Interval (0–10 per domain)	Points per domain
Global Rating of Change Scale	Ordinal	Ordinal (-7 to +7)	Points
Central Pain Processing Measures:			
Pressure Pain Threshold (PPT)	Continuous	Interval (kPa)	Pressure
Temporal Summation	Continuous	Interval (NPRS 0–10)	Points
Conditioned Pain Modulation (CPM)	Continuous	Interval (change in PPT)	Pressure

### Primary outcomes

#### Numerical Pain Rating Scale (NPRS).

The 11-point NPRS will measure shoulder pain intensity during functional activity involving arm elevation and the highest pain intensity experienced in the past week. The scale ranges from 0 (no pain) to 10 (maximum pain) and is a valid and reliable tool for assessing individuals with shoulder pain (intraclass correlation coefficient - ICC of 0.84) [42,44]. The minimum clinically significant difference (MCID) is a change of 2 points or 30% [45].

#### Shoulder Pain and Disability Index (SPADI).

The Brazilian version of the SPADI will be used to assess disability, composed of 13 questions related to two domains: disability (eight items) and pain (five items). The final score ranges from 0 to 100, with higher scores indicating greater shoulder disability [42,46]. The minimum detectable change (MDC) is 20 points or 43% of the baseline score [47].

### Secondary outcomes

#### Patient-Specific Functional Scale (PSFS).

The Brazilian version of the PSFS will be used to measure shoulder functional ability to complete specific activities. The individuals will select three to five important activities that are challenging to perform due to shoulder pain. For each reported activity, the individual will score on an 11-point scale, where 0 is (unable to perform the activity) and 10 is (able to perform the activity at the level before the injury) [48]. This scale is reliable, with an ICC of 0.91 and MDC of 1.5 points for patients with upper limb injuries [48]. Combining the scores of both SPADI and PSFS to assess individuals with shoulder pain will provide more insights into changes after treatment. The SPADI allows comparability between patients with preset questions, while the PSFS monitors changes in the most important activities impairing the function of each individual.

#### Pain Self-Efficacy Questionnaire (PSEQ).

The Brazilian version of PSEQ will be used to assess self-efficacy [49,50], which is composed of 10 items. The total score ranges from 0 to 60 points, with the higher score indicating greater self-efficacy. The scale is valid and reliable, with an ICC of 0.82 for assessing patients with chronic pain [51].

#### Pittsburgh Sleep Quality Index (PSQI).

The Brazilian version of PSQI will be used to assess sleep quality, which is composed of 19 items, resulting in a total score ranging from 0 to 21, and covering 7 domains: (1) subjective sleep quality, (2) sleep latency, (3) sleep duration, (4) habitual sleep efficiency, (5) sleep disturbance, (6) medication use and (7) dysfunction during the day [52]. The Brazilian version of PSQI is a valid and reliable tool, with a reliability coefficient of 0.82 [53].

#### Brief screening questions for biopsychosocial aspects.

The Brazilian version of Brief Screening Questions for patients with chronic pain will be used to assess biopsychosocial aspects [54], which is composed of six questions covering five domains: anxiety, kinesiophobia, stress, catastrophizing, and depression. Each question is scored on a scale from 0 to 10, with higher scores reflecting more severe symptoms [54].

#### Global rating of change scale.

The Global Rating of Change Scale will measure the individual’s perception of improvement/deterioration over time. Individuals will rate the overall change in their shoulder condition from baseline evaluation. The score ranges from -7–7, with higher scores representing a greater perception of health improvement, negative and lower scores indicating a worsening perception of health, and a score of zero representing no change [55].

#### Central pain processing.

The central pain processing will be assessed with a quantitative sensory test protocol [56] based on the modified order of the tests suggested by Gröne *et al*. 2012. The following test order will be performed: pressure pain threshold, temporal summation, and conditioned pain modulation [57]. This test order was predetermined to avoid possible carry-over effects of Conditioned Pain Modulation (cold stimulus) on other measures. Individuals will be blindfolded during those tests. A 5-minute rest will be provided between each sensory test.

i) Pressure Pain Threshold (PPT) is the minimum pressure that triggers the first pain sensation. PPT will be measured by a digital pressure algometer (AlgoMed ®, Hӧrby, Sweden) with a 1 cm^2^ circular rubber probe tip and a pressure rate of approximately 40 kPa/s, following established protocols [56,9]. Participants will be seated comfortably and instructed to maintain trunk stability during the test. The PPT test will be performed at the acromion and muscle bellies of the deltoid muscle belly (near the inferolateral insertion) and upper trapezius (halfway between the C7 spinous process and acromion process) on the affected or most affected side. PPT of a distant site from the shoulder (tibialis anterior) will also be assessed to investigate central sensitization [9]. The side for the tibialis anterior assessment will be randomly determined using a computer-generated randomization list (randomization.com). The non-painful side will be used as the remote site for participants with lower limb pain. A computer-generated randomization list will also determine the order of testing regions, stored in sealed opaque envelopes to be opened immediately before testing begins. Each site will be tested three times, with a 30-second interval between repetitions, and the average will be considered for analysis. Participants will undergo familiarization with the procedure at the lateral epicondyle. The PPT has been considered reliable, with ICC coefficients ranging from 0.82 to 0.97[58].ii) Temporal summation refers to increased perceived pain from repetitive nociceptive stimuli at the same site, which is related to the modulation mechanism occurring in second-order sensory neurons in the spinal cord [59,60]. The temporal summation will be measured at the deltoid and tibialis anterior in the same position used for the PPT testing, with a 2-minute interval between testing regions. Sequential stimulation will involve 10 pressure stimuli at the pre-established PPT level, with a one-second interval between stimuli [9,61]. Each pressure increment will be approximately 40 kPa/s [9,61]. After the first and tenth stimuli, participants will rate their pain intensity using the NPRS. The temporal summation will be quantified by subtracting the pain intensity rating for the first stimulus from the pain rating for the tenth [9,61].iii) Conditioned Pain Modulation (CPM) refers to the central nervous system’s ability to inhibit pain through mechanisms related to endogenous descending inhibition [9,62]. CPM will be assessed using the cold pressor test as the conditioning stimulus and PPT as the test stimulus. Cold pressor pain induces an effective CPM response when combined with the test stimulus of the PPT [63,64]. CPM will be evaluated in the same position used for the PPT. The participant will immerse their hand up to the wrist of the non-painful (or least painful) side [9] in ambient temperature water (22ºC) for 1 minute to standardize hand temperature [65]. Afterward, the individual will immerse the same hand in a cold-water bath (8°C) for 2 minutes. PPT at the deltoid of the affected (or most affected) side will be assessed at baseline, during immersion (after 30, 60, and 90 seconds), and after immersion (immediately post-withdrawal and at 30 and 60 seconds after withdrawal). Participants will rate their pain intensity on an 11-point NPRS every 30 seconds from immersion until hand withdrawal, and 30 and 60 seconds after withdrawal [66]. Conditioned pain modulation will be calculated by subtracting the PPT of the deltoid from PPT measures during and after CPM [62,64].

### Interventions

The interventions will last for 8 weeks, as individuals treated during this time frame have shown statistically and clinically significant improvements in previous research involving CFT [17,27] or therapeutic exercises for shoulder pain [12,13,67]. The CFT group will have one session per week, while the therapeutic exercise group will have two sessions per week. All treatment sessions will be supervised by a physiotherapist with 15 years of experience. Adherence to treatment sessions and assessments will be encouraged verbally at each session and through text messages sent the day before the scheduled appointment. In the event of absence, contact will be made by telephone to identify the reason for the absence and reschedule the session. Each session for both groups will last approximately 40–60 minutes.

Information regarding adverse effects, use of ice, heat, medication for pain, or protocol deviations reported by participants will be collected at all appointments by the physiotherapist responsible for administering the treatment and documented in the study report. An individual’s allocated intervention will be discontinued if they experience significant adverse effects related to the intervention or if they request to withdraw. The decision to discontinue the intervention will be made by the research team in a shared decision with the individual.

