### Cognitive functional therapy

CFT will be conducted once a week in individual sessions lasting approximately 60 minutes over 8 weeks. The procedures of each session will be documented by the therapists for every participant. The therapists administering CFT will undergo specific training that includes: (1) a minimum of 106 hours of CFT training with an experienced CFT tutor, and (2) analysis of videos of the therapists implementing the CFT approach by an experienced physiotherapist. CFT is structured around creating a strong therapeutic connection, using active listening alongside a motivational interviewing style that is open, reflective, and non-judgmental. This approach provides validation and employs specific strategies to reinforce the therapeutic bond between therapist and patient [68,20]. The CFT will contain:

i) Anamnesis will be conducted to evaluate the degree of pain focus, pain coping strategies, stress response, and its connection to pain their beliefs regarding pain, as well as any history of anxiety and depression, and their expectations and goals regarding the management of the shoulder pain [69].ii) Physical examination will be conducted to identify the individual’s primary maladaptive behaviors (e.g., pain-provoking, feared and/or avoided movements and/or functional tasks), that can be classified into movement impairments and control impairment. Movement impairments are characterized by movement restriction in the direction of pain and control impairments are impairments of functional control of postures and movements that can be associated with aberrant movement and postural control or muscle activity [26,70,71]. Subsequently, an approach focused on the potentially contributing factors to pain will be performed, covering the three following components [19,26]:i) Making sense of pain is a reflective process that incorporates a patient’s story and relevant life experiences, alongside their behavioral exposure outcomes. This process helps them reach a new understanding of their pain and also increases self-efficacy to accomplish personal goals.

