### Therapeutic exercises group

Individuals assigned to this group will be treated twice a week for 8 weeks. Each session will last approximately 40–60 minutes and will consist of bilateral stretching and strengthening exercises targeting the scapulothoracic and glenohumeral muscles, which are commonly associated with shoulder pain [10,11,72]. In addition, the therapist will manage symptoms by applying ischemic compression for 90 seconds, or until symptom reduction, on latent or active trigger points in the deltoid and upper trapezius, as needed. Stretching exercises will be performed in three sets of 30 seconds, with 10 seconds of rest between sets, and an intensity of maximum stretch without pain, targeting the following muscles:

i) Upper trapezius: The individuals will be instructed to flex the neck, side-bend away, and rotate towards the side to be stretched, then force down the arm on the side being stretched. This movement can be assisted and maintained during the maneuver by the contralateral hand [38,39,73].ii) Pectoralis minor: Individuals will be positioned with 90º of shoulder abduction, 90^o^ of elbow flexion, and forearm on the corner of a wall. Then, the individuals will shift the trunk forward and rotate opposite to the side being stretched [74].iii) Posterior shoulder region: the individuals will be positioned in supine and the therapist will stabilize the scapula placing one hand on the lateral edge of the scapula, and with the other hand, the therapist will perform shoulder horizontal adduction [75].

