### Harms

Adverse events and unintended effects will be collected and reported throughout the trial and to the Human Research Ethics Committee of the Universidade Federal da Paraíba. Individuals will be asked to report any side effects, which will be analyzed by the research team. All adverse events will be evaluated by their severity and potential relation to the interventions. The use of pain relief methods, such as medication, ice, or heat packs, during the study period will also be recorded.

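### Harms and co-interventions are recorded only at treatment sessions, about 16 in the exercise arm and 8 in the CFT arm, which risks unequal ascertainment

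*Protocol article*

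**What the plan says.** The Interventions section of the protocol article lists adverse effects, ice, heat, pain medication and protocol deviations as items that participants report, and names who records them and when: they "will be collected at all appointments by the physiotherapist responsible for administering the treatment". The same section sets the schedule: "The interventions will last for 8 weeks" and "The CFT group will have one session per week, while the therapeutic exercise group will have two sessions per week". The two intervention sections confirm it: "CFT will be conducted once a week in individual sessions lasting approximately 60 minutes over 8 weeks" for CFT, and "Individuals assigned to this group will be treated twice a week for 8 weeks" for exercise.

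The Harms section adds that "Adverse events and unintended effects will be collected and reported throughout the trial" and that "Individuals will be asked to report any side effects, which will be analyzed by the research team". It also says that use of pain-relief methods over the study period is recorded. It names no collector, no timetable and no route common to both arms.

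Under Blinding, only the assessor and the statistician are blinded; Strengths and limitations states that therapists and participants cannot be. The Procedures section places outcome assessments at baseline and weeks 4, 8 and 12 in both arms, but the text does not assign harms or co-intervention questions to those visits.

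**The concern.** The only collection route that the article describes is tied to the treatment schedule, and that schedule differs between the arms by design. Participants in the exercise arm are asked more often and over shorter recall intervals. Minor, short-lived complaints and occasional use of analgesics, ice or heat are the items most easily forgotten over a week, so more of them are likely to be recorded in the exercise arm. The person asking also knows the allocation, which can add error in either direction.

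What is at stake is any between-arm description of tolerability or co-intervention use in the trial report. Part of an apparent advantage for CFT, the arm hypothesised to be better, could come from the visit schedule. Co-intervention data also help in reading the pain and disability results, so unequal recording matters slightly beyond safety.

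There is a second gap. Treatment sessions end at week 8, so the only named collector has no scheduled contact in the last four weeks. Yet the Harms section covers the whole trial, and the Sample section makes a corticosteroid injection during follow-up a reason for discontinuation from the study.

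**Working it through.** The article states no number of enquiries, so there is no figure of its own to reproduce. The counts follow from its schedule.

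**Step 1: scheduled enquiries over 8 weeks**
- Exercise: 2 per week × 8 weeks = 16, one every 3.5 days on average.
- CFT: 1 per week × 8 weeks = 8, one every 7 days.
- Ratio 16/8 = 2. In weeks 8 to 12 both arms have 0.

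If the three post-baseline assessments also counted as enquiries, the totals would be 16 + 3 = 19 and 8 + 3 = 11, still unequal.

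**Step 2: what unequal enquiry could do to recorded events**

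Assumptions, none of them from the article: the true event rate is the same in both arms; events fall evenly over time; sessions are evenly spaced; each event is counted once; and the chance of reporting an event falls exponentially with the days since it happened, at rate k per day. The mean chance that an event is reported at the next session, T days after the previous one, is

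f(T) = (1 − e^(−kT)) / (kT), with f = 1 when k = 0.

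| Assumed k per day | CFT, T = 7 | Exercise, T = 3.5 | Ratio, exercise to CFT |
|---|---|---|---|
| 0 (complete recall) | 1.00 | 1.00 | 1.00 |
| 0.05 | 0.84 | 0.92 | 1.09 |
| 0.10 | 0.72 | 0.84 | 1.17 |
| 0.20 | 0.54 | 0.72 | 1.34 |

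So twice as many enquiries does not mean twice as many recorded events. Under these assumptions the excess runs from nil to about a third.

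**Step 3: why a larger figure does not follow**

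A simpler model gives every enquiry the same chance p of picking something up. At p = 0.05 the share of participants with at least one record is 1 − 0.95^8 = 34% in CFT and 1 − 0.95^16 = 56% in exercise. But this gives a 7-day and a 3.5-day window the same p, which amounts to assuming twice the detectable event rate per week in the exercise arm. If participants report everything since the last visit, the weekly CFT enquiry has pick-up chance 1 − (1 − p)^2. The chance of no record in 8 weeks is then [(1 − p)^2]^8 = (1 − p)^16 in CFT, the same as in exercise, and the ratio of the shares is 1.0.

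**The case against.** The strongest reply has four parts.

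- **No formal comparison is planned.** Harms and co-interventions are not among the listed outcomes, and the Data analysis section names no test of them. This stands and limits the weight of the point, but the data are still to be documented and evaluated, and readers will compare the arms.
- **The Harms section may cover an equal route.** It is broad enough to allow one, the schedule figure is not shown, and an article condenses its full protocol. It is therefore fair to say that the article states no route for weeks 8 to 12, and not that none exists. The unequal session-based procedure, however, is stated and not inferred from silence.
- **Therapists cannot be blinded, and the article says so.** This stands. A participant-completed form is unblinded too. The remedy addresses unequal frequency and the follow-up gap, not blinding.
- **Counts per contact would do.** They would not correct the imbalance: with complete recall and equal true events, dividing by 16 and 8 would make the exercise rate look half that of CFT. Contact counts are useful context but a poor denominator.

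A reader might infer that CFT will certainly look safer, or that the schedule alone produces risk ratios well above 1.3. The document supports neither. It gives no recall period or question wording, and the larger ratios depend on the equal-probability model rejected in the working. Events that the extra exercise sessions really cause are a treatment effect, not bias, although the stated procedure cannot tell them apart from extra questioning.

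**Conclusion.** The point holds as a risk of differential ascertainment with a likely direction: more minor events and more co-intervention use recorded in the exercise arm. The firm figures are 16 against 8 scheduled enquiries, and no treatment session in weeks 8 to 12. The effect on recorded events is not fixed by the document. It is nil with complete recall and about 1.1 to 1.3 times under assumed recall decay of 0.05 to 0.20 per day. The analysis of pain intensity and SPADI and the sample size of 72 do not depend on it. It is worth correcting because the remedy is cheap and unrecorded events cannot be recovered at analysis.

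**What to change.** Add one standard self-completed form on adverse effects, pain medication, ice and heat, and other care. Use the same questions and the same fixed recall period in both arms at the existing week 4, 8 and 12 assessments. Each arm then has 3 enquiries, and follow-up is covered. Have the form returned sealed to someone other than the assessor, since an answer could reveal the allocation.

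State in the protocol that any between-arm summary of harms and co-interventions rests on this form. Keep the therapists' session records for safety handling, and report them separately by arm with the number of contacts. Say in the Harms section which route applies in weeks 8 to 12.

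The cost is one page at each of three planned visits, with no change to treatment or sample size. Longer recall may miss some minor events. Participants who are prompted more often in sessions may also remember slightly more on the form, so the imbalance is reduced and not fully removed.
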